### Sample size calculation

2.12

Sample size estimation was performed using PASS 2021 (version 21.0.3) for a noninferiority randomized controlled trial. Based on historical data from our center, the median RFS for patients with high-risk recurrence factors managed with intensive follow-up alone was 16.1 months,^13^ corresponding to a hazard rate of 0.043 (ln(2)/16.1). Enrollment is planned over 1 year, followed by at least 2 years of follow-up. With a one-sided α of 0.025, 80% power, and a 1:1 allocation ratio, 192 participants per group (total *n* = 384) are required to demonstrate noninferiority at a hazard ratio margin of 1.4, with an estimated 139 events per group. Assuming an annual attrition rate of 5%, an additional 58 participants are required, yielding a total sample size of 442.

Sensitivity analysis was conducted using an alternative median RFS of 19.0 months derived from a cohort excluding DSA-positive patients,^34^ corresponding to a hazard rate of 0.0365 (ln(2)/19.0). Under similar assumptions, 360 and 361 participants would be required in the experimental and control groups, respectively (total *n* = 721), to achieve 80% power at the same noninferiority margin. Given the practical constraints of an investigator-initiated study without commercial funding, enrollment of more than 700 participants is not feasible; therefore, a target sample size of at least 442 participants has been selected to ensure study reliability.

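### The sensitivity sample size of 721 at a 19.0-month median does not follow from the stated inputs, which give about 420 before attrition and 441 to 493 after it

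*Protocol article*

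**What the plan says.** All the figures are in section 2.12 (Sample size calculation) of the protocol article.

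- Design: "Sample size estimation was performed using PASS 2021 (version 21.0.3) for a noninferiority randomized controlled trial".
- Base case: the median RFS for high-risk patients "managed with intensive follow-up alone was 16.1 months". Accrual lasts 1 year and follow-up at least 2 years.
- Operating characteristics: "With a one-sided α of 0.025, 80% power, and a 1:1 allocation ratio, 192 participants per group" (384 in total) "are required to demonstrate noninferiority at a hazard ratio margin of 1.4, with an estimated 139 events per group".
- Attrition: "Assuming an annual attrition rate of 5%, an additional 58 participants are required, yielding a total sample size of 442".
- Sensitivity case: "Sensitivity analysis was conducted using an alternative median RFS of 19.0 months derived from a cohort excluding DSA-positive patients". The text says the assumptions were similar, holds power at 80% and the margin unchanged, and concludes that "360 and 361 participants would be required in the experimental and control groups, respectively".
- Decision: because "enrollment of more than 700 participants is not feasible" for an investigator-initiated study without commercial funding, a target of at least 442 is adopted.

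**The concern.** In a log-rank non-inferiority calculation, the required number of events depends on the margin, alpha, power, allocation and assumed true hazard ratio. It does not depend on the median. A longer median only lowers the share of participants who have an event by the end of follow-up. Going from 16.1 to 19.0 months cuts the hazard by about 15% (1 − 16.1/19.0 = 0.153), yet the stated sample size rises by 88% (721/384 = 1.88).

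The figure matters because the enrolment target is justified by it. The reader is told that the DSA-negative scenario needs over 700 participants and that 442 is what resources allow. If 721 is wrong, that justification fails, and ethics committees and readers are given a misleading picture of how far 442 falls short.

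**Working it through.** **Inputs from section 2.12:** margin 1.4; one-sided alpha 0.025 (z = 1.960); power 80% (z = 0.842); 1:1 allocation; accrual 12 months; minimum follow-up 24 months; medians 16.1 and 19.0 months; attrition 5% per year. The true hazard ratio is not stated. I assume 1.0, because that reproduces the base case. Exponential RFS and uniform accrual are also assumed. The non-inferiority framework of section 2.12 is taken as given.

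**Step 1. Events.**
d = 4(1.960 + 0.842)² / (ln 1.4)² = 31.40 / 0.1132 = 277.3, so 278, or 139 per group as stated.

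**Step 2. Event probability.**
P = 1 − [exp(−24λ) − exp(−36λ)] / (12λ), with λ = ln 2 / median.

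**Step 3. Base case, 16.1 months.**
λ = 0.0431 and P = 0.722. N = 277.3 / 0.722 = 384.0, the stated 384. 384 × 1.15 = 441.6, the stated 442. The method therefore reproduces every base-case figure.

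**Step 4. Sensitivity case, 19.0 months.**
λ = 0.0365 and P = 0.663. N = 277.3 / 0.6626 = 418.5, so 419, or 420 in equal groups. That is 9% above 384.

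**Step 5. Adding attrition at 19.0 months.**

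| Handling of loss | N | Excess over 442 |
|---|---|---|
| 5% per year as exponential censoring (P = 0.629) | 441 | none |
| × 1.15, as the protocol does | 482 | 40 |
| ÷ 0.85 | 493 | 51 |

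None comes near 721. Freedman's event formula changes the pre-attrition figure only to 426.

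**Step 6. What 721 would imply.**
- Expected events: 721 × 0.6626 = 478. Power = Φ(ln 1.4 × √478 / 2 − 1.960) = Φ(1.72), about 96%.
- To need 721 for 80% power before attrition, one of these would have to hold: an event probability of 277.3/721 = 0.385; a margin of exp(√(31.40/478)) = 1.29; or a true hazard ratio of about 1.08.
- A margin of 1.3 with 5% per year loss as censoring gives 31.40 / (ln 1.3)² = 456.1 events, and 456.1 / 0.629 is about 725. That is close to 721, but it contradicts the statement that the margin was unchanged.
- Accrual over 36 months with no minimum follow-up, × 1.15, gives 719. That contradicts the stated accrual and follow-up.

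**Step 7. Power of 442 at 19.0 months**, from Φ(ln 1.4 × √d / 2 − 1.960):
- no loss: d = 442 × 0.6626 = 293, power 82%;
- 5% per year censoring: d = 442 × 0.6289 = 278, power 80%;
- 15% contributing nothing: d = 442 × 0.85 × 0.6626 = 249, power 76%.

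**The case against.** The best defence is that the text claims similar, not identical, assumptions and does not restate alpha, accrual or loss for the second run. PASS may have been given a different input. The margin of 1.3 in step 6 shows that this is possible, so the error may lie in a misreported input and not in a miscalculated output. That stands, and it shapes the fix. It does not rescue the paragraph, because power and margin are expressly held constant and the median is the only input said to change.

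A second defence is that 721 does not generate the target. The 442 comes from the 16.1-month calculation, which reproduces exactly, and the wrong figure errs towards pessimism. That is also true, but the feasibility sentence uses the figure to defend stopping at 442.

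Three stronger readings are tempting, and the documents do not support them.

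- **That 442 is fully adequate at 19.0 months because only 420 are needed.** The 420 is before attrition and the 442 is after it. By the protocol's own × 1.15 the comparable figure is 482, so 442 is about 40 short. Only modelling loss as censoring brings the requirement down to 441.
- **That 19.0 months should replace 16.1 as the base case because the trial randomises DSA-negative patients.** Section 2.12 ties 16.1 months to high-risk patients on intensive follow-up alone, which is the control arm. It describes the 19.0-month cohort only by its exclusion of DSA-positive patients. The Introduction, citing the same source, describes patients who received adjuvant TACE, so 19.0 months may not be a control-arm median. Each median matches the trial on a different feature.
- **That the × 1.15 inflation leaves the base case short.** Dividing 384 by 0.85 gives 452, which is 10 more than 442. Modelling 5% per year loss as censoring at 16.1 months needs only 404. The step is crude, but its error has no clear direction.

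**Conclusion.** As written, 721 is wrong for the inputs stated beside it. The like-for-like figure is about 420 before attrition and 441 to 493 after it. The shortfall of 442 in the DSA-negative scenario is 0 to about 50 participants, not the 279 (721 − 442) that the text implies, and its power there is about 76% to 82%. The claim that the alternative needs more than 700 participants therefore cannot support the choice of 442.

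This rests on a true hazard ratio of 1.0, exponential RFS and uniform accrual. None of these is stated for the sensitivity run, but together they reproduce the base case exactly. Whether the slip is in the output or in an undisclosed input cannot be settled from the document. The base-case calculation itself is not in question here.

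**What to change.** 1. Rerun the calculation at 19.0 months and publish all PASS inputs, including the true hazard ratio. Replace 721 with about 420 before attrition, and give the post-attrition figure (441 to 493) with the attrition method named. If another input was changed, such as the margin, state it and remove the claim that the margin was the same.
2. Rewrite the feasibility sentence so that it no longer rests on a requirement above 700.
3. State the power of 442 at a 19.0-month median: about 82% with no loss, 80% with 5% per year censoring, and 76% if 15% contribute nothing.
4. Keep 16.1 months as the base case unless the 19.0-month cohort is shown to be high-risk and managed without TACE.

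The cost is one software run and the rewording of one section. The correction itself requires no extra patients.

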### Statistical methods

2.13

All statistical analyses will be performed using SAS software (version 9.2). A one-sided superiority testing framework will be applied, with a significance level (α) of 0.05. Between-group comparisons will be reported with corresponding *p*-values and 95% confidence intervals. Continuous variables will be summarized as mean ± standard deviation for approximately normally distributed data, or as medians otherwise. Categorical variables will be presented as frequencies and percentages. Survival outcomes, including median RFS and OS, will be estimated using the Kaplan–Meier method with corresponding 95% confidence intervals. Group comparisons will be performed using the log-rank test, and survival curves will be generated accordingly.

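### The primary analysis is set at one-sided 0.05, twice the one-sided 0.025 used to size the trial, and does not match the 95% confidence intervals reported beside it

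*Protocol article*

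**What the plan says.** Section 2.12 (Sample size calculation) sets the design level: "With a one-sided α of 0.025, 80% power, and a 1:1 allocation ratio". It describes the calculation this way: "Sample size estimation was performed using PASS 2021 (version 21.0.3) for a noninferiority randomized controlled trial". The target is "noninferiority at a hazard ratio margin of 1.4, with an estimated 139 events per group".

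Section 2.13 (Statistical methods) sets the analysis level: "A one-sided superiority testing framework will be applied, with a significance level (α) of 0.05". The same paragraph says that comparisons between groups will be given with p-values and 95% confidence intervals, and names the log-rank test. It does not say that the interval is a one-sided bound. Nothing in the article explains why the two levels differ.

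**The concern.** Both levels are explicitly one-sided, so 0.05 cannot be read as the two-sided counterpart of 0.025. Taken literally, the rule for the primary endpoint allows twice the false-positive rate for which the trial was sized.

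The paragraph also does not fit together internally. A one-sided 0.05 test corresponds to a two-sided 90% interval, and a two-sided 95% interval corresponds to a one-sided 0.025 test. The trial could therefore announce a positive result while its own 95% interval includes no effect. Two readers of the same data could reach different conclusions, each citing the protocol.

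This matters more than usual here because the trial is meant to settle a disagreement between guidelines. Section 2.16 also plans an interim analysis of RFS, and alpha cannot be allocated to that look until the total is unambiguous.

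**Working it through.** **Inputs** (Section 2.12 unless stated)
- Noninferiority margin: HR 1.4. The true HR is taken as 1, an assumption that reproduces the stated events.
- Design alpha one-sided 0.025 (z = 1.960); power 80% (z = 0.8416); 1:1 allocation.
- Events: 139 per group, 2 × 139 = 278 in total.
- Control median RFS 16.1 months, hazard ln(2)/16.1 = 0.0431 per month; 12 months of accrual and at least 24 months of follow-up.
- Analysis alpha one-sided 0.05 (z = 1.645), from Section 2.13.

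**Step 1: reproduce the plan's own figures.** Schoenfeld's formula for total events is 4(z_α + z_β)² / (ln HR)².
- At one-sided 0.025: 4(1.960 + 0.8416)² / (ln 1.4)² = 277.3, rounded up to 278, or 139 per group. This matches exactly.
- With exponential RFS and uniform accrual, P(event) = 1 − (e^(−24h) − e^(−36h)) / (12h) = 0.722 at h = 0.0431. Then 278 / 0.722 = 385, against the stated 384.

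**Step 2: repeat at the analysis alpha.**
- At one-sided 0.05: 4(1.645 + 0.8416)² / (ln 1.4)² = 218.4, rounded up to 219 events. This implies about 303 participants before attrition.

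The sample size therefore rests on 0.025, and 0.05 does not reproduce it. The ratio is 0.05 / 0.025 = 2.

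**Step 3: success thresholds at 278 events.** SE(log HR) ≈ 2/√278 = 0.120. The superiority cut-off is exp(−z × SE), and the noninferiority cut-off is 1.4 times that.

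| One-sided alpha | Superiority: observed HR below | Noninferiority: observed HR below | Matching two-sided interval |
|---|---|---|---|
| 0.025 | 0.790 | 1.107 | 95% |
| 0.05 | 0.821 | 1.149 | 90% |

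**Step 4: an example of the disagreement.** For an observed HR of 0.805, z = −ln(0.805)/0.120 = 1.81 and the one-sided p = 0.035, a success at 0.05. The two-sided 95% interval is 0.636 to 1.018 and includes 1. The upper limit of the 90% interval is 0.981. Under no effect, the chance of landing in this zone is 0.05 − 0.025 = 0.025.

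**Step 5: what the stricter level costs in power at 278 events.** The article states no superiority effect, so the superiority rows are illustrative.

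| True HR and hypothesis | Power at 0.025 | Power at 0.05 |
|---|---|---|
| 1.00, noninferiority (margin 1.4) | 80.1% | 87.7% |
| 0.75, superiority | 66.9% | 77.4% |
| 0.80, superiority | 46.0% | 58.5% |

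**The case against.** The strongest reply is that this is the smaller half of a larger contradiction. The two levels are attached to different hypotheses: noninferiority in Section 2.12 and superiority in Section 2.13. Aligning alpha alone leaves that conflict open. No superiority test was sized at all, and the noninferiority figures at 0.05 combine one section's level with the other's hypothesis. This is fair as a limit on what the correction achieves. It does not remove the point, because the level is doubled whichever hypothesis is kept and choosing a hypothesis would not settle alpha.

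A second reply is that one-sided 0.05 may be a slip for two-sided 0.05, which would agree with both Section 2.12 and the 95% intervals. That is plausible, but the text would need the same correction.

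A third reply is that a two-sided 95% interval beside a one-sided test is not an error in itself, and that a one-sided 95% bound would match. The article does not say that such a bound is meant. It is true that the disagreement is narrow: it arises only for a one-sided p between 0.025 and 0.05, where the estimate still favours TACE and the 95% interval only just crosses 1.

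Finally, the correction is not free if superiority is kept, as the power figures show. That stands and is counted in the cost.

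**Conclusion.** The point holds, and the text is wrong as written. The analysis alpha in Section 2.13 is exactly twice the design alpha in Section 2.12, and the stated 278 events reproduce only at one-sided 0.025. Following Section 2.13 allows a declared success for observed hazard ratios of about 0.790 to 0.821 although the 95% interval includes 1.

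The thresholds assume about 278 events at analysis, equal allocation and SE(log HR) ≈ 2/√278. The statement about intervals assumes the usual two-sided 95% interval. The factor of two needs none of these assumptions. Because this is the decision rule for the primary endpoint of a phase III trial, it must be corrected before the analysis.

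**What to change.** In Section 2.13, replace 0.05 with one-sided 0.025 as the total alpha for RFS, less any alpha spent at the RFS interim in Section 2.16. State that this is equivalent to judging the hazard ratio by its two-sided 95% confidence interval, so that test and interval use the same level.

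The edit is one line and leaves the 278 events and the stated sample size intact. Its price is a stricter threshold: for superiority, an observed HR of 0.790 instead of 0.821. If noninferiority is kept, power stays at the designed 80%, slightly lower if alpha is spent at the interim. If superiority is kept, power falls, for example from 77.4% to 66.9% at an illustrative true HR of 0.75. Keeping one-sided 0.05 instead would mean redoing Section 2.12 and reporting 90% intervals.

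The choice between noninferiority and superiority must be settled separately; this edit does not do it.

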#### Sequence generation

2.9.1

Randomization will be performed using computer-generated random number tables managed by Good Clinical Practice-compliant research centers at participating sites. Personnel responsible for sequence generation will have no involvement in study conduct. The interval between randomization and administration of adjuvant TACE will not exceed 1 week. During angiography, if tumor staining is identified in the remnant liver, TACE will be performed for clinical management; however, such participants will be excluded from the study.

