### Additional analyses

2.14

Predefined subgroup analyses of RFS will be conducted according to clinically relevant prognostic factors, including age, ECOG PS, tumor stage, tumor rupture, maximum tumor diameter, tumor multiplicity, microvascular invasion, Vp1/Vp2 portal vein invasion, lymph node metastasis, surgical margin status, and histologic differentiation grade.

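### The RFS comparison is a plain log-rank test that leaves recorded prognostic factors unused; it is valid, but under the stated superiority framework it gives up power that a prespecified adjusted analysis would recover

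*Protocol article*

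**What the plan says.** Section 2.13 of the protocol article (Statistical methods) gives the framework: "A one-sided superiority testing framework will be applied, with a significance level (α) of 0.05". For survival outcomes it specifies Kaplan–Meier estimates and one between-group test: "Group comparisons will be performed using the log-rank test". It names no strata, covariates or hazard-ratio model.

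Section 2.9.1 (Sequence generation) says "Randomization will be performed using computer-generated random number tables". Neither it nor the sections on concealment and implementation mention stratification factors, although section 2.2 plans more than ten hospitals.

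The eligibility criteria (section 2.6.1) admit a patient with any one of eight high-risk factors, from rupture and large diameter to nodal metastasis and poor differentiation. Section 2.14 (Additional analyses) lists eleven prognostic factors for RFS subgroups, including "maximum tumor diameter, tumor multiplicity, microvascular invasion, Vp1/Vp2 portal vein invasion, lymph node metastasis, surgical margin status, and histologic differentiation grade". No other use of them is stated.

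Section 2.12 sizes the trial in a different framework: "Sample size estimation was performed using PASS 2021 (version 21.0.3) for a noninferiority randomized controlled trial". Its inputs are "With a one-sided α of 0.025, 80% power, and a 1:1 allocation ratio" and "noninferiority at a hazard ratio margin of 1.4, with an estimated 139 events per group".

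**The concern.** Because any one of eight dissimilar factors suffices for entry, recurrence risk is likely to vary widely between patients. The factors come from surgery and its pathology, so they are on record before randomization, and the article itself treats them as prognostic. The stated comparison does not use them.

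When a treatment effect exists and outcome depends on recorded covariates, a test that ignores them has less power than one that conditions on them. That matters here because section 2.12 says enrollment above 700 is not feasible. If the sample cannot grow, covariates already collected are the cheapest source of precision for the superiority test of section 2.13. Adjustment also accounts for chance imbalance in a strong factor in the trial actually run.

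**Working it through.** **Inputs from the documents.** Margin 1.4, one-sided 0.025, 80% power, 1:1 allocation; control median RFS 16.1 months; 12 months of accrual and at least 24 months of follow-up; 5% annual attrition; N = 442 (all section 2.12). Superiority at one-sided 0.05 (section 2.13).

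**Step 1: reproduce the plan's figure.** Schoenfeld's formula with a true hazard ratio of 1 (not stated, but it reproduces the figure):

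- Events = 4 × (1.960 + 0.842)² / (ln 1.4)² = 31.40 / 0.1132 = 277.3, so 278, or 139 per group as stated.
- Hazard ln 2 / 16.1 = 0.0431 per month. With uniform accrual over 12 months and 24 months minimum follow-up, the event probability is 0.722, and 277.3 / 0.722 = 384, as stated.
- 384 × 1.15 = 441.6, so 442, as stated.

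This calculation contains no covariates. The stated 80% is therefore not overstated by the choice of a plain log-rank test.

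**Step 2: superiority power with and without adjustment.** Assumptions not in the documents: a conditional hazard ratio of 0.75, and a normally distributed prognostic log-hazard score with SD 0.3 to 1.0. One SD of the score then multiplies the hazard by e^0.3 = 1.35, e^0.5 = 1.65, e^0.8 = 2.23 or e^1.0 = 2.72. Each setting used 1,500 simulated trials of 442 patients, with the overall control median held at 16.1 months, 5% annual attrition, and the accrual and follow-up above. The unadjusted analysis is a Cox Wald test of treatment alone, approximately the log-rank test. The adjusted analysis adds the score. The Monte Carlo standard error of a power near 75% is √(0.75 × 0.25 / 1500) = 1.1 points; both analyses use the same simulated data.

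| SD | HR unadjusted | HR adjusted | Power unadjusted | Power adjusted | Difference (points) |
|---|---|---|---|---|---|
| 0.3 | 0.760 | 0.752 | 74.5% | 77.7% | 3.2 |
| 0.5 | 0.770 | 0.748 | 69.9% | 76.4% | 6.5 |
| 0.8 | 0.793 | 0.751 | 59.4% | 73.9% | 14.5 |
| 1.0 | 0.809 | 0.750 | 53.3% | 75.4% | 22.1 |

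A second set-up replaced the score with five binary factors (assumed prevalences 15–40%, true hazard ratio 0.72, one-sided 0.05, 700 trials, Monte Carlo standard error 1.3 to 1.6 points). Unadjusted against adjusted power was 82% against 85% with factor hazard ratios of 1.25, 85% against 87% with 1.5, and 76% against 86% with 2. The direction is the same: small with weak factors, about 10 points with strong ones.

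**Step 3: the noninferiority design of section 2.12.** True hazard ratio 1, margin 1.4, one-sided 0.025, same simulation:

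| SD | Power unadjusted | Power adjusted |
|---|---|---|
| 0.3 | 81.8% | 82.4% |
| 0.5 | 80.9% | 82.0% |
| 0.8 | 80.9% | 80.3% |
| 1.0 | 80.5% | 79.6% |

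Both hazard ratios are about 1.00, and the differences, about 1 point either way, are of the order of the simulation error. Adjustment gains nothing material here.

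**The case against.** The strongest reply is that nothing here is wrong. A log-rank test is a valid primary test, it matches the covariate-free calculation that set N, and its type I error already allows for chance imbalance. The article never calls the test unadjusted, and covariates or strata may stand in a full protocol or SAP that is not shown. The size of the loss rests wholly on assumed factor strengths: five independent factors at a hazard ratio of 2 each imply a 32-fold range in hazard (2⁵). The simulations also adjust for exactly the true prognostic variables, which a real model would capture only in part.

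Most of this stands, and it makes the point an efficiency recommendation. It does not remove it: the article states which test it will use, and under its own superiority framework a better one is available from data already collected. If another document specifies adjustment, section 2.13 should say so.

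A reader might go further and infer two things that the documents do not support.

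- **That the unadjusted hazard ratio is biased toward 1.** A log-rank test yields no hazard ratio. The value nearer 1 from an unadjusted Cox model is the marginal hazard ratio, a different estimand from the conditional one.
- **That the plain analysis inflates false noninferiority claims.** If the true conditional hazard ratio is 1.4, the unadjusted analysis does declare noninferiority in 3.9% to 13.6% of simulated trials, against 1.9% to 2.9% with adjustment. That is an error only if 1.4 was meant as a conditional margin. Section 2.12 gives the margin with a single population median and no covariates, and does not say so. With the marginal hazard ratio set near 1.4, the unadjusted rate was 1.9% to 3.3% over 1,200 trials, about nominal.

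**Conclusion.** The point holds as a loss of efficiency under the superiority framework of section 2.13. At one-sided 0.05 and an assumed conditional hazard ratio of 0.75, the plain log-rank test gives up about 3 points of power with weak factors (SD 0.3), 6 to 7 points at SD 0.5 and about 15 points at SD 0.8. The direction is secure whenever there is a real effect and the factors are prognostic; the size is not, because the documents give no factor effects or prevalences.

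Under the noninferiority design of section 2.12 with a true hazard ratio of 1, the gain is about nil. Whether the point matters therefore depends on which framework governs. Sections 2.12 and 2.13 disagree on both the hypothesis and alpha (noninferiority at 0.025, superiority at 0.05). That conflict is the weightier problem and has to be settled first.

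**What to change.** Once the framework is settled as superiority, make the primary RFS comparison a Cox model of treatment, or a covariate-adjusted or stratified log-rank test, with a short list of factors fixed before unblinding. Maximum diameter, multiplicity, microvascular invasion, Vp1/Vp2 invasion and margin status are natural candidates. Keep the unadjusted log-rank test and Kaplan–Meier curves as supporting analyses. A named Cox model would also supply a hazard ratio for the 95% confidence intervals that section 2.13 promises for between-group comparisons, which a log-rank test alone does not give. Stratifying by centre is optional; no gain from it has been shown.

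The cost is a sentence or two in section 2.13. The factors are already needed for eligibility and subgroups, and N need not change. The downside is that the adjusted hazard ratio is conditional on the listed factors. If noninferiority against 1.4 is tested, the plan should state the scale on which the margin is set, or report the marginal hazard ratio for that test.
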